#### Diet quality

The Dietary Questionnaire for Epidemiological Studies (version 2) (DQES), developed by the Cancer Council of Victoria
[53], will be used to assess dietary habits. The DQES is a 96-item questionnaire designed to assess food intake over the previous 12-months, and takes approximately 30-45 minutes to complete. It contains 74 items for which participants indicate how frequently they would have consumed the item on a 10-point scale ranging from “0 - Never” to “10 - 3 or more times per day”. Included in the questionnaire are three photographs of scaled portions of four foods and questions regarding the frequency of fruit and vegetable intake and other foods which do not readily fit the aforementioned intake frequency format (e.g. added sugar, breads and cheese). The 74 food items are separated into four groups: cereal foods, sweets and snacks; dairy products, meat and fish; fruit; and vegetables. Consumption of alcoholic beverages is assessed by a separate set of questions. The DQES has been validated for use in mid-age Australian women and young Australian adults
[54].

To account for sweetened drink intake (soft-drink, sports drinks, energy drinks, fruit drinks and cordial) which is not assessed by the DQES, participants will be asked to fill out a 6-item questionnaire. For each sweetened drink category (full sugar soft-drink; sports/energy drinks; and fruit drinks/cordial) participants are to indicate, on average, how often they had consumed the drink in the previous 12-months on a 10-point scale using the same frequency increments as in the DQES. Participants will also indicate, when they consumed the drink, how much they usually consume on a 3-point scale consisting of “One glass (250 mL)”, “One can (375 mL)” or “One bottle (600 mL)”. Output data from the DQES will be amended post-hoc to account for nutrient contribution attributable to the intake of sweet drinks.

#### Fitness

Cardiovascular fitness is to be assessed by a three minute walk test, performed at a self-regulated intensity of RPE-13. Walking distances will then be used to predict maximal oxygen consumption (VO_2max_) using the equation of Cao et al.
[55] which is strongly correlated with objectively measured maximal oxygen consumption (R = 0.84, SEE = 4.57mL▪kg^-1^▪min^-1^) during maximal incremental cycle tests.

#### Sleep quality

Aspects of sleep quantity and quality will be assessed using questions four and six from the Pittsburgh Sleep Quality Index
[56], while questions from Maislin and colleagues
[57] will be used as an indicator of sleep disordered breathing symptomatology.

#### Correlates of physical activity

Exercise self-efficacy and the salient aspects of the physical environment will also be assessed from questions adapted from Nigg and Riebe
[58] (barrier self-efficacy), Schwarzer and colleagues
[59] (relapse self-efficacy) and De Bourdeaudhuij, Sallis and Saelens
[60] (physical activity environment).

#### Demographics

Basic demographics including age, gender, ethnicity, highest attained education, occupation and marital status, as well as perceived general health, family history of disease and smoking status will be collected using a customised questionnaire.

### Statistical considerations

#### Sample size

A priori power calculations indicated 106 participants are required per group (n = 212) to detect a medium effect size (Cohen’s d = 0.5), at 80% power, with significance level set at α = 0.05 and the assumption that the predictors will contribute an R^2^ of 0.5. Given a 30% attrition rate from a recent pilot study (unpublished) a total sample size of 300 will be targeted.

#### Statistical plan

Data will be collated and manipulated using Microsoft Excel 2010 (Microsoft Corporation, Redmond, WA). Statistical analyses will be performed using STATA Data Analysis and Statistical Software version 12 (StataCorp LP, College Station, TX) and SPSS version 21 (IBM corp., Armonk, NY). Significance levels will be set at α = 0.05. Distributions of all variables will be assessed using the Shapiro-Wilk test, with appropriate normalization procedures applied where required. Independent samples t-tests will be performed on baseline measures to test for differences in demographic outcomes. Change scores for all outcomes will be calculated and compared between randomisation groups using parametric or non-parametric analyses as appropriate for the data distributions. Random effects mixed modelling will be used with time (0, 12, 26 and 52 weeks) and group allocation (Intervention and Control) as the fixed factors. A time by group interaction term will be used to formally test the aims of the study.

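### The formal mixed-model test uses baseline inefficiently, and a second set of change-score tests, with the method chosen from the data, has no stated role

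*Protocol article*

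**What the plan says.** The Statistical plan sets two between-group analyses.

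- **Change scores.** "Change scores for all outcomes will be calculated and compared between randomisation groups using parametric or non-parametric analyses as appropriate for the data distributions". Before this, "Distributions of all variables will be assessed using the Shapiro-Wilk test, with appropriate normalization procedures applied where required".
- **Mixed model.** Time (weeks 0, 12, 26 and 52) and group are the fixed factors. The last sentence of the section makes their interaction the formal test of the study's aims. No baseline covariate or other predictor is listed.

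One significance level covers everything: "Significance levels will be set at α = 0.05".

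The Sample size section rests on "the assumption that the predictors will contribute an R^2^ of 0.5" without naming the predictors. It also states "Given a 30% attrition rate from a recent pilot study (unpublished) a total sample size of 300 will be targeted". Under Outcome measures, the primary outcomes are daily minutes in three intensity bands. Under Randomisation and blinding, participants with complex medical conditions who are judged to need closer monitoring are placed in the Intervention group rather than randomised.

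**The concern.** **Use of baseline.** With week 0 as a response and each group free to have its own week-0 mean, the interaction compares change from baseline. That fixes the weight on baseline at 1, whatever the correlation between visits. Estimating the weight gives a more precise treatment effect from the same data.

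**A second inferential analysis without a role.** The change-score comparison covers all outcomes and compares the randomised groups, but the plan does not say whether it is supportive, descriptive or co-primary. If each of the three primary intensity outcomes were tested at each of three follow-up visits, that would make nine tests beside the formal one.

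**A test chosen from the data.** The distribution check is applied to the variables, not to model residuals. A rank test on change, a difference on a transformed scale and a mean difference in minutes per day answer different questions. Which one is reported would be settled only after the data are seen.

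**No counterpart for the R².** The sample size counts on predictors that do not appear in the stated model.

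**Working it through.** **1. The plan's own figure.** Inputs from the Sample size section: "106 participants are required per group (n = 212" in total), "to detect a medium effect size" (d = 0.5), "at 80% power, with significance level set at" 0.05, and R² = 0.5. Sidedness is not stated; two-sided is assumed here. With f the variance relative to a single measurement,

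n per group = 2(1.960 + 0.842)² f / d² = 62.8 f.

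- No use of R² (f = 1): 63
- R² as a variance reduction (f = 0.5): 32
- R² as a variance inflation (f = 2): 126
- One-sided, same three cases: 50, 25 and 99

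None gives 106. The nearest match is 104, from 95% power with no R², but the article states 80%. The attrition step is consistent: 212/0.70 = 303, close to 300, and 300 × 0.70 = 210 completers.

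**2. Equivalence of the two contrasts.** Time as a factor, group and their interaction give every group-by-visit cell its own mean. With complete data the week-12 interaction contrast is therefore

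(mean week 12 − mean week 0) in Intervention − (mean week 12 − mean week 0) in Control,

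which is the difference in mean change scores. In 60 simulated complete datasets (four visits, random intercept, correlation 0.707) the two estimates agreed to about 10⁻¹⁴. The standard error was 0.105, against 0.097 with baseline as a covariate: (0.105/0.097)² = 1.17.

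**3. Variance factors.** Let ρ be the correlation between baseline and follow-up, with equal variance at both visits. The article gives no ρ, so a range is shown; ρ = 0.707 corresponds to R² = 0.5 if baseline were the only predictor.

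- Change score or interaction contrast: 2(1 − ρ)
- Baseline-adjusted: 1 − ρ²
- Ratio: 2/(1 + ρ)

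| ρ (assumed) | Change | Adjusted | Ratio | n per group, change / adjusted | Power at 106, change / adjusted |
|---|---|---|---|---|---|
| 0 | 2.00 | 1.00 | 2.00 | 126 / 63 | 73.0% / 95.4% |
| 0.3 | 1.40 | 0.91 | 1.54 | 88 / 58 | 86.8% / 96.8% |
| 0.5 | 1.00 | 0.75 | 1.33 | 63 / 48 | 95.4% / 98.8% |
| 0.707 | 0.586 | 0.500 | 1.17 | 37 / 32 | 99.7% / 99.9% |

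Power is Φ(d√(n/(2f)) − 1.96), with d on the scale of the outcome SD, one follow-up visit and individual randomisation.

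Ignoring baseline altogether gives f = 1.00. Below ρ = 0.5 the change contrast is therefore less precise than follow-up values alone (1.40 against 1.00 at ρ = 0.3).

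Taking square roots of the ratios, confidence intervals are about 24%, 15% and 8% wider than with baseline adjustment at ρ = 0.3, 0.5 and 0.707.

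**4. Where 80% power would be lost.** Setting 62.8 × 2(1 − ρ) = 106 gives ρ ≈ 0.16. Only below that does the change contrast at 106 per group fall short of 80%.

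**5. When the two planned analyses can differ.** With complete data and a parametric test they give the same week-12 estimate. They can part company through a rank test, a transformation, missing visits (a change score needs both values, while the mixed model uses every available visit), or an overall interaction across visits set against a change at one visit.

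**The case against.** **The plan names its formal test.** This stands. A reader might infer that there are two equal answers per outcome with nothing to choose between them. The last sentence of the Statistical plan rules that out: the hierarchy is incomplete, not absent. What remains open is the role and form of the change-score tests.

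**The model does use baseline.** This stands too. It would be wrong to say that baseline is ignored. Modelling baseline as a response is a standard, valid method, and the criticism is of efficiency only.

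**The power is ample.** A reader might infer that the analysis has 17% more variance than the sample size assumed, or that the trial is underpowered as a result. Neither is supported. The figure of 106 does not follow from R² = 0.5 (that would need 32 per group, or 63 with no R²), so no planned precision can be read from it. With no R² gain, 106 per group gives about 95% power under individual randomisation. The predictors are also unnamed, and the Background speaks of psychological, social and environmental predictors of sustained response, so they need not be baseline values.

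**Details may be left to an analysis plan.** Covariates, missing-data handling and diagnostics often are. But the article does state the fixed factors, and it does state that the test will follow the distributions. The point rests on those statements. The article does not say that change scores will be complete-case, and back-transformation could restore minutes per day, so neither is treated as a settled fault.

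**Conclusion.** The point holds as a matter of precision and of pre-specification. The stated interaction contrast has 1.54, 1.33 and 1.17 times the variance of a baseline-adjusted contrast at ρ = 0.3, 0.5 and 0.71. Put the other way, adjustment multiplies the variance by (1 + ρ)/2, a saving of 35%, 25% and 15%. These figures assume complete data, equal variances at the two visits, individual randomisation and a ρ that the article does not give.

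The stated 80% power is not shown to fail. The change-score tests leave an avoidable choice of method and scale open until the data are seen, although a formal test is named. The assumed R² has no counterpart in the stated model. The plan should be changed on these points, but it is not invalid. That 106 does not follow from its inputs, and that the article describes cluster randomisation, are separate matters not argued here.

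**What to change.** 1. Keep the mixed model as the single formal analysis and adjust it for baseline. Either enter baseline as a covariate with weeks 12, 26 and 52 as responses, or keep week 0 as a response and constrain its mean to be equal across arms.
2. Do this in randomised participants only. Participants placed in Intervention without randomisation give no ground for assuming equal baseline means.
3. Report adjusted differences in minutes per day. Replace the Shapiro-Wilk-driven choice of test with checks of model residuals, and specify robust or bootstrap standard errors in advance for skewed outcomes.
4. Label the change-score comparisons descriptive or supportive. If any test of them is kept, fix it in advance.
5. Name the predictors behind the R² of 0.5 and put them in the model, or drop the assumption and redo the sample size.

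Items 1 to 4 need only a change of analysis wording, and baseline is already measured. Item 5 needs a short recalculation. Any separate analysis plan should say the same.

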## Methods/Design

### Participants and setting

The REACH study is a randomised controlled intervention trial. Approximately 300 participants will be recruited from rural South Australia and randomised into either the Intervention or Control group. Table 
1 outlines the inclusion and exclusion criteria for the study. For the purposes of this study, ‘rural’ is defined as a Remoteness Area, identified by the Australian Bureau of Statistics (ABS), as predominantly outer regional, remote or very remote. The Riverland and Yorke Peninsula regions of South Australia have therefore been selected as recruitment regions. According to the ABS, 86.3% and 83.1% of the Riverland
[22] and Yorke Peninsula
[23] are classed as outer regional, respectively, satisfying the aforementioned criteria. The Riverland has an approximate population of 42,000 people
[22] and an average Socio-Economic Indexes for Areas (SEIFA) score of 914.14
[24], indicating an area of relative socio-economic disadvantage. The Yorke Peninsula has an approximate population of 27,500
[23] people and an average SEIFA score of 924.44
[24], indicating similar socio-economic disadvantage. The dominant employment sectors of these two regions are indicative of those associated with rural Australia, with the main employment sector in the Riverland being fruit and nut tree growing
[25], while dry land farming (crops and livestock) serves as the dominant employment sector in the Yorke Peninsula
[26].

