### Protocol

#### Testing procedure

All participants will attend four baseline sessions, each one week apart. Session one will last approximately 20 minutes, while the remaining sessions will last approximately 60 minutes. At the first session, held during the evening, participants will be provided with an accelerometer and instructed in the correct measurement protocol. During session two, to be held early in the morning, health measures (anthropometry, blood pressure and blood chemistry) will be taken and participants will complete a dietary questionnaire. At the end of this session, participants will be provided with, and instructed in, the use of a Salivette saliva sampling kit. Session three, held during the afternoon, will comprise the completion of a further three questionnaires assessing psychological wellbeing, sweet-drink intake and general health/demographics. All questionnaires will be self-administered using a computer-based survey system. Two three-minute walking tests will also be completed. Session four, performed at baseline only, provides an information session for the participants about the details of the intervention, designed separately for Intervention and Control groups. The Control group will be instructed on the importance of participating in regular physical activity as per the Australian Physical Activity Guidelines

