[10], how to setup and use their pedometer (Yamax DW700; Yamasa Tokei Keiki Co. Ltd., Tokyo, Japan) and tips for incorporating physical activity into daily life. The Intervention group, in addition to the information provided to the Control group, will be shown how to use the REACH website, including how to log their steps and other information. Measures will be repeated following the 12-weeks of the intervention period, and at 6-months and 12-months follow-up (i.e. 3-months and 9-months from end of the intervention). Participants will be recruited from three intervention regions: the Riverland; the Copper Coast (Upper Yorke Peninsula); and the Lower Yorke Peninsula. In each location, testing sessions will be provided in four different towns on different days. This is to minimise participant burden by providing a number of opportunities to participate around their usual schedule and reduce distances needed to travel. Testing will begin in the Riverland, followed by the Copper Coast and then the Lower Yorke Peninsula. Testing in the second and third regions will begin during the information session (session four) of the preceding region.

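### Free improvement: add region and region-by-time to the mixed model and stratify the allocation by region; the gain is small unless towns were allocated without regional balance

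*Protocol article*

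**What the plan says.** The Statistical plan section names the structure of the formal model. "Random effects mixed modelling will be used with time" opens the sentence, which goes on to list "time (0, 12, 26 and 52 weeks) and group allocation (Intervention and Control) as the fixed factors". The next sentence fixes the test: "A time by group interaction term will be used to formally test the aims of the study". The level of the random effects (participant, town or region) is not given. The same section also compares change scores between the groups and names no adjustment for region.

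The Testing procedure section describes the geography and timing. "Participants will be recruited from three intervention regions: the Riverland; the Copper Coast (Upper Yorke Peninsula); and the Lower Yorke Peninsula". They are taken in order: "Testing will begin in the Riverland, followed by the Copper Coast and then the Lower Yorke Peninsula". The overlap is defined: "Testing in the second and third regions will begin during the information session (session four) of the preceding region". Each region has testing sessions in four towns.

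The Participants and setting section gives fruit and nut tree growing as the main employment sector in the Riverland, while "dry land farming (crops and livestock) serves as the dominant employment sector in the Yorke Peninsula".

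The Randomisation and blinding section says that a cluster randomisation technique is used. It names neither the unit nor any stratification or balancing by region.

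**The concern.** Region is a design factor known for every participant before allocation. Because the regions start at different times, a given study week falls on a different calendar date in each. The primary outcomes are whole-day activity times recorded over a full week, so they include activity at work, and the main kind of work differs between the Riverland and the Yorke Peninsula. It is plausible that change from baseline differs somewhat by region for reasons unrelated to the intervention.

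A model with only time, group and their interaction imposes one time course on all regions. Two consequences are possible:

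- Region-specific changes add to the residual variance and widen the confidence interval.
- If the arms are unevenly spread over the regions, part of the regional change is counted in the time-by-group term, which is the formal test of the trial's aims.

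The first applies under any allocation that has both arms in each region, and is small. The second depends on how the clusters were allocated, which the article does not say.

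**Working it through.** **Inputs from the article.** Three regions, four towns each, so 3 × 4 = 12 towns. "All participants will attend four baseline sessions, each one week apart", so session four comes 3 × 1 = 3 weeks after session one. The second region therefore starts about 3 weeks after the first, and the third about 6 weeks after. The planned effect is d = 0.5 (Sample size section).

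**Assumptions.** The article gives no figure for regional or seasonal change, so none can be reproduced. I assume that the mean change differs between regions by -s, 0 and +s, in units of the within-region SD of change, with equal region sizes. For the town-level case I also assume that 6 of 12 equal-sized towns go to Intervention.

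**1. Precision, with allocation balanced over regions.** The between-region variance of the change is (s² + 0 + s²)/3 = 2s²/3. The share of variance that a region-by-time term removes is (2s²/3)/(1 + 2s²/3), and the standard error falls by the factor 1/√(1 + 2s²/3).

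| s | 2s²/3 | variance removed | SE reduction |
|---|---|---|---|
| 0.1 | 0.0067 | 0.7% | 0.3% |
| 0.2 | 0.0267 | 2.6% | 1.3% |
| 0.3 | 0.0600 | 5.7% | 2.9% |

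**2. Shift in the estimate, with towns drawn without stratification.** Let a and c be the numbers of Intervention towns in the +s and -s regions. The Intervention mean is s(a - c)/6. The Control mean is s[(4 - a) - (4 - c)]/6 = -s(a - c)/6. The spurious difference is therefore s(a - c)/3. With two Intervention towns in every region, a = c and the difference is zero.

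There are C(12,6) = 924 possible draws:

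| Absolute value of (a - c) | Size of shift | Draws | Share |
|---|---|---|---|
| 0 | 0 | 248 | 27% |
| 1 | s/3 | 384 | 42% |
| 2 or more | 2s/3 or more | 292 | 32% |

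By symmetry, 292/2 = 146 draws (16%) give 2s/3 or more in favour of Intervention. At s = 0.3, 2s/3 = 0.20 SD, which is 0.20/0.5 = 40% of the planned effect if d is read on the same SD scale.

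**3. Simulated type I error.** The simulation compares change scores under no intervention effect, with 210 completers, 70 per region, 3,000 runs per case and a nominal level of 5%. No correlation within towns was simulated beyond the regional shift.

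| Allocation | s = 0.3: without → with region | s = 0.5: without → with region |
|---|---|---|
| Individual | 5.3% → 5.2% | 4.9% → 5.2% |
| Towns, balanced within region | 4.5% → 5.0% | 3.2% → 4.1% |
| Towns, no stratification | 16.9% → 5.2% | 30.8% → 5.4% |
| Whole regions, 2 against 1 | 57.5% → not estimable | 68.4% → not estimable |

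Under individual allocation the mean standard error falls from 0.142 to 0.138 (3%) at s = 0.3 and from 0.149 to 0.139 (7%) at s = 0.5. In the last row group is fully determined by region, so a region term cannot be separated from group.

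**The case against.** The strongest case against is that this is a short paragraph in a journal article. Covariates and random-effect levels are often left to a fuller document, and the unspecified random effects neither state nor exclude a town or region effect. That limits the point but does not remove it. The sentence positively lists the fixed factors, region is not among them, and the suggestion improves a stated method.

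Several stronger readings are tempting, and the documents do not support them.

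- A reader might infer that sequential regions by themselves bias the comparison. They do not. A regional or seasonal shift shared by both arms within a region cancels from the time-by-group contrast, and the simulation shows nominal error under individual allocation. The large seasonal movement over 0 to 52 weeks is also common to both arms and falls in the time term.
- A reader might think that all regional differences remain in the error. Stable differences in level are removed by change scores, or by a participant random effect if one is used. Only region-specific change remains.
- A reader might count the draws in which at least one region splits 3:1 or worse, 1 - 216/924 = 77%, and take that as the chance of serious bias. Many of those draws give a shift of s/3 or none. The share reaching 2s/3 is 32%, in either direction.
- A reader might picture three distinct farming regions. Two of the three lie on the Yorke Peninsula, for which the article gives one dominant sector. It also describes the Riverland and the peninsula as similar in remoteness (86.3% and 83.1% outer regional) and in disadvantage (SEIFA 914.14 and 924.44). The lag of about 3 weeks per region is short.

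It is also fair to say that imbalance from a random draw of towns averages to zero over draws. It is extra between-cluster variation, and belongs mainly to the separate question of naming and modelling the cluster. In the trial as run, however, only one draw is made, and stratification prevents the regional part of that imbalance.

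**Conclusion.** This is a free improvement and not an error that invalidates the analysis. If allocation is individual or balanced within region, omitting region causes no bias, and the loss is about 0.3% to 3% of the standard error for s between 0.1 and 0.3. If towns are allocated without regional stratification, the omission matters more: a shift of 2s/3 or more in 32% of draws and none in 27%. Simulated type I error is then 17% to 31% without region and about 5% with it, for s of 0.3 to 0.5.

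These sizes rest on an assumed three-step gradient, equal regions and towns, and town as the unit of allocation. The article confirms none of these. It does establish the staggered regions, the two listed fixed factors, and the absence of any statement that allocation is balanced by region. It does not establish that an imbalance exists or that activity changes differently by region.

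**What to change.** In Randomisation and blinding, state that allocation is stratified by region, so that both arms are present in each. With towns as clusters, this means two of four towns per arm in every region. In the Statistical plan, add region (Riverland, Copper Coast, Lower Yorke Peninsula) and region-by-time as fixed effects in the mixed model for every outcome.

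The cost is 2 degrees of freedom for region and 2 × 3 = 6 for region-by-time, 8 in all, against at most 300 × 4 = 1,200 observations. No new data are needed, because region is already known for each participant.

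Two limits should be stated with the change. The region terms do not account for correlation within the randomised clusters, so the unit of randomisation still has to be named and carried in the model. If whole regions are the clusters, no region term can separate region from group, so only the allocation part of this change would help.
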